**Methods:**

The study will be a single-blinded, parallel-group, randomized controlled trial conducted at the Dermatology outpatient department of Acharya Vinoba Bhave Rural Hospital Sawangi Meghe, Wardha, from March 2023 to September 2025. Eligible participants diagnosed with hand eczema will be randomized into two groups: Group 1 will receive Clobetasol Propionate 0.05% ointment, and Group 2 will receive Tofacitinib 2% ointment. The primary outcome measure is the change from baseline in the Hand Eczema Severity Index (HECSI) score, assessed at two weeks and four weeks. Statistical analysis will utilize appropriate parametric and non-parametric tests, with a p-value <0.05 considered significant.

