### Objectives

1.To evaluate the efficacy of topical tofacitinib 2% ointment in hand eczema.2.To evaluate the efficacy of topically applied clobetasol propionate 0.05% ointment for hand eczema.3.To compare the effect of topically applied tofacitinib 2% ointment and topically applied clobetasol propionate 0.05% ointment in hand eczema.4.To study the side effects of topical clobetasol propionate 0.05% ointment and topical Tofacitinib 2% ointment.

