### Sample size

Effect of topical tofacitinib for hand eczema = 81.7%

Effect of topical steroid for hand eczema = 68%

Clinically significant at (δ) = 25%

$$N={\left(1.64+0.84\right)}^{2}*\left(0.817\right)\;\left(1–0.817\right)+0.68\;\left(1-0.68\right)/{\left(0.25\right)}^{2}=36$$

Sample size = 36

Total sample size = 72 (36 per group)

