### Statistical analysis

The statistical analysis for this comparative study between topical Tofacitinib 2% ointment and topical Clobetasol Propionate 0.05% ointment in managing hand eczema will encompass a comprehensive approach utilizing appropriate parametric and non-parametric tests. The primary focus will be on the change from the baseline of the Hand Eczema Severity Index (HECSI) score. In the initial stage, descriptive statistics will be employed to summarize the baseline characteristics of participants in both treatment groups. Continuous variables will be presented as mean and standard deviation (or median and interquartile range), while categorical variables will be expressed as frequencies with percentages.

The comparative analysis will be conducted using an independent t-test or Mann-Whitney U test for the primary outcome—change from baseline in HECSI score. The choice between tests will depend on the data distribution, and statistical significance will be determined with a threshold of p<0.05. After the primary analysis, subgroup analyses may be undertaken to explore potential variations in treatment response based on age, gender, and baseline severity. Safety and adverse events will be summarized, and the incidence rates between the two treatment groups will be compared using Chi-square or Fisher’s exact test.

The handling of missing data will be addressed, potentially utilizing multiple imputations to enhance the robustness of the results. Sensitivity analyses may be performed to assess the impact of outliers or influential data points on the overall findings.

Exploratory analyses will investigate potential relationships between treatment response and additional factors, such as patient demographics or specific characteristics of hand eczema. Statistical software such as R Studio Version 4.3.1 will execute these analyses.

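### The sample size uses a one-sided 5% critical value, but the analysis sets p<0.05 with no one-sided test stated; read as two-sided, the plan's own formula gives about 70% power, not the implied 80%

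*Protocol article*

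**What the plan says.** The Sample size section gives three inputs: "Effect of topical tofacitinib for hand eczema = 81.7" per cent, "Effect of topical steroid for hand eczema = 68" per cent, and "Clinically significant at (δ) = 25" per cent. It places these in a formula whose leading term is the square of 1.64 plus 0.84, and concludes "Total sample size = 72 (36 per group". It writes neither a significance level nor a power; both have to be read from the two normal quantiles.

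The Statistical analysis section names an "independent t-test or Mann-Whitney U test for the primary outcome", which is change from baseline in HECSI, and adds that "statistical significance will be determined with a threshold of p<0.05". The Methods paragraph of the Abstract repeats the threshold: "with a p-value <0.05 considered significant". Neither place says whether the test has one side or two.

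The third objective is "To compare the effect of topically applied tofacitinib 2% ointment and topically applied clobetasol propionate 0.05% ointment in hand eczema". It states no direction. The article contains no one-sided hypothesis and no non-inferiority margin.

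**The concern.** A sample size and the test it supports should use the same type I error. Here the calculation uses the critical value for 5% in one tail. The analysis quotes 5% with no qualification, for two tests that are conventionally reported two-sided, under an objective that favours neither ointment. If the analysis follows that convention, the trial was sized at a two-sided level of about 10% and will be judged at 5%.

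What is at stake is how a null result is read. A reader who takes the 0.84 at face value would think that a true 25-point difference had a 20% chance of being missed. By the plan's own formula, at two-sided 5%, that chance is about 30%.

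**Working it through.** **Inputs** (all from the Sample size section unless noted)

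- Assumed rates: p1 = 0.817 (tofacitinib), p2 = 0.68 (steroid)
- Target difference: δ = 0.25
- Normal quantiles: 1.64 and 0.84
- n = 36 per group
- Significance threshold: p<0.05, sidedness not given (Statistical analysis; Abstract, Methods)

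**What the quantiles mean.** 2 × (1 − Φ(1.64)) = 0.101, so 1.64 is one-sided 5% or two-sided 10.1%. Φ(0.84) ≈ 0.80, so the implied power is 80%.

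**Reproducing the plan's figure.** The formula is n = (z_α + z_β)² × [p1(1 − p1) + p2(1 − p2)] / δ². The square brackets are needed: taken literally as printed, the expression gives 4.4.

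- Variance sum: 0.817 × 0.183 + 0.68 × 0.32 = 0.1495 + 0.2176 = 0.3671
- (1.64 + 0.84)² = 2.48² = 6.1504
- n = 6.1504 × 0.3671 / 0.0625 = 36.13

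This reproduces the stated 36, so 1.64 is the value that produced the sample size.

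**Same formula with the two-sided 5% value.**

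- (1.96 + 0.84)² = 2.80² = 7.84
- n = 7.84 × 0.3671 / 0.0625 = 46.05, that is 47 per group, 94 in total

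**Power at the planned 36 per group.**

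- SE = √(0.3671 / 36) = 0.1010; δ / SE = 2.476
- One-sided 5%: Φ(2.476 − 1.645) = 79.7%
- Two-sided 5%: Φ(2.476 − 1.96) = 69.7%

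**Difference detectable with 80% power at 36 per group, two-sided 5%.** 2.80 × 0.1010 = 0.283, about 28 points.

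**Sensitivity to the variance.** The formula takes its variances from 81.7% and 68%, which are 13.7 points apart, yet uses a difference of 25 points. Taking rates that really differ by 25 points, with a pooled variance under the null, gives at 36 per group:

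| Rates | One-sided 5% | Two-sided 5% |
|---|---|---|
| 93% vs 68% | 86.2% | 77.5% |
| 81.7% vs 56.7% | 75.1% | 63.7% |

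The level moves with the rates chosen, but in each row the two-sided figure is roughly 9 to 11 points below the one-sided one.

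**The case against.** The strongest reply is that the article never says the test is two-sided. A t-test or Mann-Whitney U test can be run either way, and some of the text leans towards tofacitinib: the Introduction speaks of its possible advantages, the Expected Outcome paragraph considers a result in its favour, and the assumed rates put it ahead. With a one-sided 5% test, 36 per group gives 79.7%, and the calculation and the threshold agree. This stands in part. A reader might infer that the analysis is two-sided as a matter of record; the document supports that only as the conventional reading of an unqualified p<0.05. But an expectation of benefit is not a test specification and the objective is neutral, so the sidedness has to be stated whichever was meant.

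A second reply is that 70% is not the power of the primary analysis. This stands fully. A reader might take the figure as the chance that the planned test succeeds. It is not: the planned test is on change in HECSI, no standard deviation or mean difference is given for it, and its power cannot be computed. The 70% belongs to the plan's own formula for two proportions.

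Two further readings go too far. One is that the arithmetic is wrong; with the brackets supplied it reproduces 36, and going from 36.13 to 36 is immaterial. The other is that an allowance for dropout is missing; the article gives no dropout rate, and a condensed article may leave this to the full protocol.

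The mismatch cannot be left to an unseen analysis plan. The critical value and the threshold are both printed in this article, and nothing printed reconciles them.

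**Conclusion.** The point holds on a stated condition. The sample size rests on one-sided 5% and an implied 80% power, while the analysis declares significance at p<0.05 with no one-sided hypothesis. Under the usual two-sided reading, 36 per group gives 69.7% by the plan's own formula for a 25-point difference, a loss of about 10 points.

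This rests on four assumptions: p<0.05 is read as two-sided; the 80% is inferred from 0.84, since no power is written; the 25-point target is accepted as given; and the plan's variance sum of 0.3671 is used, where rates truly 25 points apart would give 63.7% to 77.5%. It says nothing about the power of the HECSI comparison.

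**What to change.** In the Statistical analysis section, state that the primary test is two-sided at the 5% level. In the Sample size section, replace 1.64 with 1.96. Because the formula would then return 47 while the trial keeps 36, present the calculation as power at a fixed n. For example:

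*With 36 participants per group and a two-sided 5% test, a two-proportion normal approximation with variances from response rates of 81.7% and 68% gives about 70% power for a 25-point difference, or 80% power for a difference of about 28 points. This concerns a binary response and is not the power of the primary comparison of change in HECSI, for which no standard deviation or mean difference has been assumed.*

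Brackets should be added around the variance sum at the same time. If the sponsor did intend a one-sided 5% test, the alternative is to say so, with its direction, and keep 1.64.

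The cost is a few sentences and a stated power about 10 points lower. No extra patients are needed. The Study status section says the trial has not started, so the change can precede enrolment. If 80% at two-sided 5% is wanted for 25 points, the same formula asks for 47 per group (94 in total against 72); that is the sponsor's choice and not part of this fix.

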### Statistical analysis

The statistical analysis for this comparative study between topical Tofacitinib 2% ointment and topical Clobetasol Propionate 0.05% ointment in managing hand eczema will encompass a comprehensive approach utilizing appropriate parametric and non-parametric tests. The primary focus will be on the change from the baseline of the Hand Eczema Severity Index (HECSI) score. In the initial stage, descriptive statistics will be employed to summarize the baseline characteristics of participants in both treatment groups. Continuous variables will be presented as mean and standard deviation (or median and interquartile range), while categorical variables will be expressed as frequencies with percentages.

The comparative analysis will be conducted using an independent t-test or Mann-Whitney U test for the primary outcome—change from baseline in HECSI score. The choice between tests will depend on the data distribution, and statistical significance will be determined with a threshold of p<0.05. After the primary analysis, subgroup analyses may be undertaken to explore potential variations in treatment response based on age, gender, and baseline severity. Safety and adverse events will be summarized, and the incidence rates between the two treatment groups will be compared using Chi-square or Fisher’s exact test.

The handling of missing data will be addressed, potentially utilizing multiple imputations to enhance the robustness of the results. Sensitivity analyses may be performed to assess the impact of outliers or influential data points on the overall findings.

Exploratory analyses will investigate potential relationships between treatment response and additional factors, such as patient demographics or specific characteristics of hand eczema. Statistical software such as R Studio Version 4.3.1 will execute these analyses.

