### Inclusion criteria

1.Patients providing written consent before the initiation of any treatment.2.Clinically diagnosed cases of hand eczema of all grades as per the Hand Eczema Severity Index (HECSI) score.3.Age above 18 years.4.No prior treatment for hand eczema in the past 1 month.

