### Enrollment

1.
**Recruitment:** The recruitment process will commence at the Dermatology outpatient department (DVL) of AVBRH Sawangi Meghe, Wardha, from March 2023. A designated study coordinator will identify potential participants based on clinical diagnosis and eligibility criteria. Eligible patients will be provided with detailed information about the study, and the purpose, risks, and benefits will be explained.2.
**Informed consent:** Written and signed informed consent will be obtained from all eligible patients willing to participate in the study. The consent form will include information about the nature of the study, potential risks and benefits, confidentiality assurances, and the voluntary nature of participation.3.
**Screening and inclusion/exclusion criteria:** Eligible participants will undergo a screening process to confirm their clinical diagnosis and ensure they meet the inclusion criteria while excluding those who meet any exclusion criteria. The study coordinator will collect relevant medical history and conduct a thorough examination to confirm the diagnosis of hand eczema.4.
**Baseline assessments:** Baseline assessments will include the collection of demographic information, medical history, and baseline Hand Eczema Severity Index (HECSI) scores. Clinical photographs of affected areas will be taken during followup visits for documentation and comparison.5.
**Randomization and allocation:** After obtaining informed consent and confirming eligibility, participants will be assigned to either Group 1 (Clobetasol Propionate) or Group 2 (Tofacitinib) through computer-generated randomization. Age and gender cross-matching will be performed to ensure balanced groups.6.
**Assignment of interventions:** Participants will be provided with the assigned treatment (topical Clobetasol Propionate 0.05% ointment or topical Tofacitinib 2% ointment) along with detailed instructions for application.7.
**Follow-up appointments:** Participants will be scheduled for followup visits at 2 weeks and 4 weeks after the initiation of treatment. The study coordinator will communicate the importance of attending all followup appointments and the need for adherence to the assigned treatment.8.
**Monitoring adherence:** Adherence to the assigned intervention will be monitored through self-reporting, return of unused medications, and documentation during followup visits.9.

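### The primary test ignores baseline HECSI and is picked from the data, which can cost substantial power and leaves the effect measure unfixed

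*Protocol article*

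**What the plan says.** - **Primary test** (Statistical analysis): "The comparative analysis will be conducted using an independent t-test or Mann-Whitney U test for the primary outcome", applied to change from baseline in HECSI.
- **Choice of test** (same section): "The choice between tests will depend on the data distribution, and statistical significance will be determined with a threshold of p<0.05". No criterion is given.
- **Outcome** (abstract, Methods): "The primary outcome measure is the change from baseline in the Hand Eczema Severity Index (HECSI) score, assessed at two weeks and four weeks". Two time points are listed, and neither place says whether change is absolute or percent.
- **Who enters** (Inclusion criteria): "Clinically diagnosed cases of hand eczema of all grades as per the Hand Eczema Severity Index (HECSI) score". There is no minimum score.
- **What is recorded before treatment** (Enrollment, baseline assessments): "baseline Hand Eczema Severity Index (HECSI) scores".
- **Comparative use of baseline severity** (Statistical analysis): only that "subgroup analyses may be undertaken to explore potential variations in treatment response based on age, gender, and baseline severity".
- **Balancing** (Allocation; Enrollment): by age and gender, not by severity.
- **Size** (Sample size): 36 per group, 72 in total, derived from percentages and not from HECSI change.

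**The concern.** With no severity floor, absolute change is bounded by the starting score: a patient who starts at 8 points cannot fall by 40. If improvement is roughly proportional, much of the spread in change is then spread in baseline. A two-sample test on change leaves that variance in the error term, although the covariate that would remove it is measured in everyone.

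The t-test and the Mann-Whitney test also answer different questions. The first compares mean change; the second compares the ordering of changes. If the choice waits for the data, the quantity to be estimated and reported is not known in advance.

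At stake are the power of a trial with 36 patients per arm and the clarity of its main result.

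**Working it through.** **1. The plan's own figure.** With a bracket around the variance sum, the Sample size formula gives (1.64 + 0.84)² × [0.817 × 0.183 + 0.68 × 0.32] / 0.25² = 6.1504 × 0.3671 / 0.0625 = 36.1, so the stated 36 per group reproduces. It contains no HECSI SD or correlation, so it cannot show what the HECSI analysis gains or loses.

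**2. Closed form.** Let σ be the baseline SD, k the ratio of week-4 SD to baseline SD, and ρ their correlation. None of these is in the protocol; the values below are assumptions.

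- Variance of change: σ²(1 + k² − 2ρk)
- Residual variance under ANCOVA: σ²k²(1 − ρ²)
- With k = 1 the ratio of the second to the first is (1 − ρ²) / [2(1 − ρ)] = (1 + ρ)/2

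| k | ρ | ANCOVA / change | Ratio | 36 per arm works like |
|---|---|---|---|---|
| 1 | 0.3 | 0.91 / 1.40 | 0.65 | 55 |
| 1 | 0.5 | 0.75 / 1.00 | 0.75 | 48 |
| 1 | 0.7 | 0.51 / 0.60 | 0.85 | 42 |
| 1 | 0.9 | 0.19 / 0.20 | 0.95 | 38 |
| 0.6 | 0.3 | 0.3276 / 1.00 | 0.33 | 110 |
| 0.6 | 0.5 | 0.27 / 0.76 | 0.36 | 101 |
| 0.6 | 0.7 | 0.1836 / 0.52 | 0.35 | 102 |

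The last column is 36 divided by the ratio. With k = 1, if the change-score test had 80% power, ANCOVA would have 94%, 90%, 86% and 82% at ρ = 0.3, 0.5, 0.7 and 0.9. The lower rows (k = 0.6) matter if both active treatments shrink the scores and hence their spread.

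**3. Simulation of absolute change, proportional response.** Assumptions: 36 per arm; lognormal baseline with log-mean 3.6; log of the week-4/baseline ratio with mean −0.9 and SD 0.5; a further −0.35 in one arm; two-sided 0.05; 4,000 replicates. Power:

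| Baseline log-SD | t on change | Mann-Whitney on change | ANCOVA | ANCOVA, log scale | t on percent change |
|---|---|---|---|---|---|
| 0.3 | 51% | 49% | 75% | 84% | 79% |
| 0.7 | 19% | 25% | 62% | 82% | 78% |

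Repeat runs moved these by a point or two.

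**4. A second set of assumptions.** Here the Sample size percentages (81.7% and 68%) are read as mean proportional reductions. Reductions are beta-distributed with precision 4 or 8, baseline is lognormal with median 40 (capped at 360), and the test is chosen by Shapiro-Wilk in each arm. Power of the planned test on absolute change against ANCOVA on the original scale:

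- log-SD 0.3: 49–58% against 80–96%
- log-SD 0.6: 22–23% against 72–92%
- log-SD 0.9: 14–15% against 60–83%

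ANCOVA on the log scale gave 89–99%, and an unadjusted t-test on percent change 84–99%.

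**5. Type I error.** With no true difference and the test chosen by Shapiro-Wilk, rejection was between 4.7% and 5.4% across all null runs under both sets of assumptions.

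**The case against.** Several replies have force.

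- **The planned analysis is conventional and valid.** This stands. Randomisation protects the unadjusted comparison. A reader might infer that the result is biased by whichever arm draws more severe cases. Chance imbalance in baseline is already part of the variance of the change score; it is the same power loss, not a further bias.
- **Two candidate tests need not inflate error.** A reader might infer two chances at significance. The protocol does not support that: "The choice between tests will depend on the data distribution", not on the p-values. Selection by a normality test kept type I error at about 5%. Without a criterion there is room for misuse, but misuse is not the plan.
- **Baseline spread may not dominate.** A reader might infer that it overwhelms the treatment effect. The protocol gives nothing from which to show this, and with equal SDs and ρ = 0.9 adjustment saves only 5% of the sample.
- **Absolute change is not stated.** It is the natural reading, but percent change would remove most of the dependence on baseline. In step 3 the unadjusted t-test on percent change even beat ANCOVA on the original scale. The unstated scale is therefore part of the problem. The simulations also suit the log-scale model, because the data were generated multiplicatively.
- **An analysis plan may supply the detail.** It could add a normality criterion, and the missing criterion alone would not be worth raising. But the protocol names the two unadjusted tests, so a plan using ANCOVA would depart from it.

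**Conclusion.** The point holds as one of efficiency and definition, not of validity. The stated primary analysis leaves out a covariate that is collected in every patient, in a trial that enrols all severities, and lets the data decide which effect is estimated.

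The textual facts are certain; the size of the loss is not. It runs from 5% of the sample (equal SDs, ρ = 0.9) to about two thirds (week-4 SD 0.6 of baseline, ρ 0.3–0.7). For absolute change with proportional response, the step 3 simulations give roughly 18–51% power unadjusted against 62–84% adjusted, depending on baseline spread. If change is analysed as a percentage, the gap largely disappears. It should be corrected, but it would not invalidate the trial.

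**What to change.** The Study status section says that the trial has not started, so the primary analysis can still be fixed before any data exist.

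- **One model:** ANCOVA of HECSI, or of log(HECSI + 1), on treatment with baseline HECSI on the same scale as covariate. Decide the scale now. Add any factors actually used to balance the allocation (age and gender, if the cross-matching is kept).
- **One time point:** name which of the two listed visits is primary; the other becomes secondary.
- **Reporting:** the adjusted difference, or the adjusted ratio on the log scale, with a 95% confidence interval.
- **Sensitivity analysis:** Mann-Whitney on change, with absolute or percent change stated. It no longer competes for the primary role.

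The cost is a change of wording in the Statistical analysis section and the matching lines of the abstract. No new data, visits or patients are needed.

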### Interventions

**Group 1 (Control): Topical Clobetasol Propionate 0.05% Ointment.** Patients in this group will receive topical Clobetasol Propionate 0.05% ointment as their treatment modality for hand eczema. They will be instructed to apply the ointment twice daily over the affected areas. The treatment duration will extend for 4 weeks.

**Group 2 (Experimental): Topical Tofacitinib 2% Ointment.** Patients in this group will receive topical Tofacitinib 2% ointment as their treatment modality for hand eczema. Similar to Group 1, they will be instructed to apply the ointment twice daily over the affected areas. The treatment duration will also be 4 weeks.

**Application instructions:** Patients in both groups will be educated on properly applying the assigned ointments. They will be instructed to wash their hands before applying a thin layer of the ointment evenly on the affected areas, avoiding contact with eyes and mucous membranes. Patients will be advised not to bandage or cover the treated areas unless directed by the investigator. Additionally, they will be instructed to avoid excessive sun exposure and use sunscreen on treated areas.

**Follow-up visits:** Participants from both groups will be scheduled for followup visits at 2 weeks and 4 weeks after the initiation of treatment. During these visits, clinical photographs will be taken with the patient’s informed consent, and the Hand Eczema Severity Index (HECSI)
^
5
^ score will be recorded to assess the efficacy and side effects of the respective interventions.

**Monitoring:** The study will be monitored to ensure adherence to the assigned interventions, proper data collection, and participant safety. Adverse events, if any, will be documented and reported. Regular communication with participants will be maintained to address any concerns or queries they may have during the study.

**Adjustments:** Any deviations from the study protocol will be documented, and appropriate measures will be taken to address them. Adjustments will be made in consultation with the Institutional Ethics Committee if necessary.

**Blinding:** The study will be single-blinded, with the participants unaware of their assigned treatment group. This helps minimize bias in reporting outcomes.

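### The primary test named for HECSI change does not adjust for baseline and ignores the week-2 score of a patient missing week 4, with imputation only a possibility; a baseline-adjusted repeated-measures model would do better at almost no cost.

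*Protocol article*

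**What the plan says.** Statistical analysis, on the primary outcome: "The comparative analysis will be conducted using an independent t-test or Mann-Whitney U test for the primary outcome", namely change from baseline in HECSI. On which test applies: "The choice between tests will depend on the data distribution". On the criterion: "statistical significance will be determined with a threshold of p<0.05". No covariate is named for this comparison; baseline severity appears only under possible subgroup analyses.

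On missing scores, the section says that they will be dealt with, "potentially utilizing multiple imputations to enhance the robustness of the results". No other method for missing data is named.

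On timing, the Methods part of the Abstract has the primary outcome "assessed at two weeks and four weeks", and Interventions schedules "followup visits at 2 weeks and 4 weeks after the initiation of treatment". Baseline HECSI is recorded at enrolment. The trial will therefore hold three scores on a patient who completes, and two on a patient who is seen at week 2 and then leaves. The Statistical analysis section does not say which visit decides; week 4 is taken as the deciding visit below.

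**The concern.** A two-sample test on change at week 4 uses one number per patient. Baseline enters it with a coefficient fixed at 1, through the subtraction, and not with the coefficient that the data support. The week-2 score does not enter at all, so a patient seen at week 2 and lost by week 4 contributes nothing unless the score is imputed, and imputation is only a possible step.

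Two things are at stake. The first is precision, in a trial of 36 per arm whose sample-size line shows no allowance for loss. The second is bias: if patients doing poorly at week 2 leave one arm more often, those still present at week 4 are a selected group in that arm, and the week-2 score that would reveal this goes unused.

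The non-parametric branch adds a practical point. Rubin's rules pool an estimate with its variance. A U statistic or its p-value is neither, so an analyst who lands on Mann-Whitney after imputing has an extra step to take, and the article does not mention it.

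**Working it through.** **Sample size.** The Sample size section gives 36 per group from rates of 81.7% and 68%, a difference of 25%, and z values of 1.64 and 0.84. With the variances bracketed together:

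n = (1.64 + 0.84)² × [0.817 × 0.183 + 0.68 × 0.32] / 0.25² = 6.1504 × 0.3671 / 0.0625 = 36.13.

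The stated 36 reproduces. It is used below only as the number per arm.

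**Precision from the week-2 score.** Assume a fraction m missing at week 4 equally in both arms, and correlation r between week 2 and week 4. Completers give 36(1 − m). Using week 2 gives about 36 / [1 + (m/(1 − m))(1 − r²)].

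- m = 0.15, r = 0.7: completers 30.6; using week 2, 36 / (1 + 0.1765 × 0.51) = 33.0.
- m = 0.15, r = 0.5 or 0.9: 31.8 or 34.8, against 30.6.
- m = 0.05, r = 0.7: 35.1 against 34.2.
- m = 0.25, r = 0.7: 30.8 against 27.0.

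**Precision from baseline.** If baseline and change correlate at c in size, adjustment multiplies the SD of the estimated difference by about √(1 − c²): 0.95 at c = 0.3, 0.87 at 0.5, 0.71 at 0.7. A simulation at 36 per arm, with improvement assumed proportional to baseline, gave an SD of 2.7 points with baseline adjustment and week 2, against 5.1 to 5.4 for the unadjusted comparison. The ratio, 0.50 to 0.53, corresponds to c of about 0.85 to 0.87. Halving is therefore the favourable end, reached when patients with higher scores fall by proportionately more points.

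**Bias if imputation is not used.** Assumed inputs:
- baseline median 50;
- mean week-4 improvement 70% on clobetasol and 13.7 percentage points more on tofacitinib (81.7 − 68, used here only as a scale);
- SD 20 percentage points; week-2 to week-4 correlation 0.7;
- clobetasol patients below 35% improvement at week 2 leave with probability p = 0.45, and everyone else with 0.05.

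Missing is then 17.5% against 5%. Over 4,000 simulated trials the mean difference (negative favours tofacitinib) was −8.15 with full data, −6.66 in completers and −8.15 using week 2. The completers' figure is 1.49/8.15 = 18% too small. With no true effect, completers gave +1.53 and the week-2 analysis +0.02.

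A hand check shows how this moves with p. From 17.5 = 5 + 40q, the share of poor week-2 responders is q = 0.3125, where the normal density is 0.354. Completers' mean week-2 score in that arm shifts by 0.354(p − 0.05) / [0.95 − q(p − 0.05)] SDs. Multiply by 0.7 × 20 percentage points and by a mean baseline of 8.1/0.137 = 59.1:

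- p = 0.45: 0.1416/0.825 = 0.172 SD, then 2.40 percentage points, then 1.4 HECSI points, close to the simulated 1.5.
- p = 0.25 (11.3% missing in that arm): 0.7 points.
- p = 0.15 (8.1% missing): 0.3 points.
- p = 0.05 (no excess): 0.

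**Can imputation and Mann-Whitney be combined?** Take θ = U/(n₁n₂) with its DeLong-type variance in each of M imputed data sets, and pool: θ̄ is the mean, and T = mean variance + (1 + 1/M) × between-imputation variance. With 36 per arm, M = 20, 1,500 replicates, imputation from arm, baseline and week 2, and poor week-2 responders leaving one arm:

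- No effect, about 24% missing in that arm: mean θ was 0.502 (full data), 0.464 (completers) and 0.502 (pooled). Two-sided 5% rejection was 6.1%, 8.3% and 5.6%.
- An assumed effect, about 13% missing: θ was 0.323, 0.301 and 0.322; rejection was 75.7%, 80.7% and 75.4%.

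The pooled analysis follows the full data; the completers' analysis does not.

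**The case against.** A reader might infer that multiple imputation and Mann-Whitney cannot be combined, so that the primary result is forced back on completers. The documents do not support that. The t-test is the first test named, and its mean difference and standard error pool directly. Mann-Whitney pools through U/(n₁n₂) and its variance, as shown above. No section makes completers the analysis set, drops imputation when the rank test is chosen, or bars week-2 HECSI from the imputation model. The imputation model and pooling rule commonly sit in an analysis plan, which is not shown here, so their absence is not a fault. All of this stands.

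It can also be said that an unadjusted two-sample test is valid under randomisation, and that with complete data it is unbiased. That stands too: baseline adjustment is a gain in efficiency, not the repair of an error.

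On bias, participants are stated to be unaware of their group, so knowing that one drug is long established cannot itself drive them to leave. This weakens the case for strongly one-sided loss. It does not remove it, because poor response is a reason to leave whether or not the drug is known, and blinding is stated only for participants. The dropout pattern in the simulations is chosen, and with no excess loss in either arm the bias is zero. The rejection rate of 8.3% against 6.1% is a modest change even at about 24% missing in one arm.

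None of this reaches the narrower point. The primary test is a choice that the article does fix, and that test as stated does not adjust for baseline or use week 2.

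**Conclusion.** The point holds as one of method choice. The primary test as fixed leaves information unused that the trial will already hold, and it is protected against selective loss only if the optional imputation is carried out with the earlier scores.

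The firmest part is precision. Using week 2 is worth about 2.4 patients per arm at 15% missing and a correlation of 0.7 (33.0 − 30.6), and from 0.9 to 3.8 as missingness runs from 5% to 25%. Baseline adjustment may be worth much more, from a 5% to roughly a 50% cut in the SD of the estimate, depending on how closely change follows baseline. The possible bias, about 0.3 to 1.5 HECSI points, arises only with one-sided loss of poor responders and only if imputation is not used. HECSI distribution, correlations, effect and dropout are all assumed, because the documents give none of them on the HECSI scale.

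The plan's two named methods do not conflict. What remains of that issue is narrow: U or its p-value cannot go straight into Rubin's rules.

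**What to change.** In the Statistical analysis section, replace the primary two-sample test with a repeated-measures model for HECSI at weeks 2 and 4. Include arm, visit, arm-by-visit and baseline HECSI-by-visit, in all randomised patients with any follow-up score. Report the adjusted arm difference with a 95% CI at the deciding visit, and name that visit. If residuals are skewed, use a bootstrap interval for the same difference instead of switching to a rank test.

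If multiple imputation is kept, impute week 4 from arm, baseline and week-2 HECSI, and pool the baseline-adjusted mean difference with its standard error.

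The cost is a few sentences and slightly more programming in R, with no new data or visits. The Study status section says the trial has not begun, so the change can be made before any data are seen. The downside is reliance on a missing-at-random assumption: loss must be explained by arm, baseline and week-2 HECSI. The model also recovers nothing for a patient with no follow-up score.
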